### Power analysis

We assume a sample of 500, (one cluster based on single-site setting), testing 4 interventions in a full factorial design (16 groups), and testing of main effects and 2-way interactions. Also, we assume a baseline measure of the outcome to be used as a covariate and a correlation between pre- and post-measures of 0.65 (as assumed in Dziak, Nahum-Shani, and Collins [50]). Given a sample size of 500, a main effect of size 0.191 can be detected with 80% power and an interaction effect of 0.382 can be detected with 80% power. Thus, with a sample size of 500 we can detect small main effects (less than 0.2) and interaction effects that are between small and moderate (0.2 to 0.5) [51].

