### Active living counseling

Lifestyle interventions are capable of producing significant, long-lasting increases in physical activity [30]. We will utilize a lifestyle counseling intervention based on the Active Living Every Day program (ALED). ALED is grounded in the Transtheoretical Model and Social Cognitive Theory and has been demonstrated as an effective intervention for increasing physical activity across several populations [30–32]. The lifestyle counseling program will consists of 12 in-person group educational sessions, facilitated by project interventionists. Participants randomized to this intervention will attend 12 bi-weekly sessions. Interventionists will be trained in delivery of the ALED program. These sessions will involve discussion of topics related to increasing physical activity, including: identifying and overcoming barriers, setting goals, social support, and time management.

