## Statistical analysis

The goal of identifying the most effective components of physical activity intervention will be accomplished through the MOST design in which the four interventions (supervised exercise, facility access, self-monitoring, and active living counseling) each at two levels (presence, absence) are included for a total of 16 combinations (see Table 1). The 500 participants will be divided into one of the 16 combinations for about 31 participants per combination. Note that some participants receive more than one intervention so that half the sample (*n* = 250) receives each intervention. All participants completing baseline and at least one post-baseline assessment will be used in the analysis.

To accomplish the analytical goals, a linear mixed-effects model (using SAS Proc Mixed), will be conducted with MVPA as the outcome and with time (3 months and 6 months) as the within-subjects factor and intervention (i.e., supervised exercise, facility access, self-monitoring, and active living counseling) as the between subjects factor, along with all two-way interactions. Baseline minutes of MVPA, age, BMI, race/ethnicity, socioeconomic status, and education will be included as covariates, along with other relevant demographic and clinical characteristics (e.g., disease stage, treatment, time since diagnosis) collected through participant self-report and data available through the UT Southwestern Cancer Registry. The model will allow for random intercepts while all other factors will be fixed effects.

If MVPA is not sufficiently normally distributed, a log transformation will be used. If the log transformation does not sufficiently normalize the data then non-parametric methods or non-linear models will be considered. As recommended in Collins, et al [47–49], effect coding (− 1, 1) of the interventions will be used instead of dummy coding (0, 1). Main effects and interactions will be estimated for the 3 month and 6 month assessments. Effects will be considered significant if p < = 0.05. The goodness of fit of the final model will be assessed.

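### Active living counselling is taught in groups, but neither the model nor the power calculation allows for correlation within a class, so that component's precision and power are optimistic if such correlation exists

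*Protocol article*

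**What the plan says.** Under Active living counseling, the protocol article describes this component as "12 in-person group educational sessions, facilitated by project interventionists". Social support is among the topics. Under Statistical analysis, each component is allocated "so that half the sample (*n* = 250) receives each intervention".

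The same section fixes the random structure of the MVPA model: "The model will allow for random intercepts while all other factors will be fixed effects". Time is the within-subjects factor, so the natural reading is one intercept per participant. It also sets one threshold for every effect: "Effects will be considered significant if p < = 0.05".

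The Power analysis section deals with clustering in a parenthesis, "one cluster based on single-site setting". The end of Statistical analysis justifies a single-site approach by the fact that all delivery takes place at one centre. On that basis the article states that "a main effect of size 0.191 can be detected with 80% power" and that "an interaction effect of 0.382 can be detected with 80% power". It mentions no class size, ICC, design effect or class term.

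**The concern.** Having a single site removes clustering between sites. It does not remove clustering between classes within the site. Women who attend counselling together share discussion, group support and possibly a facilitator, so their later activity may be correlated. Women without the component attend no class. This is a partially nested design: one half of the counselling contrast may be clustered and the other half is not.

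A participant intercept absorbs the correlation between one woman's 3- and 6-month values. It does nothing for correlation between women. Even if the intercept were meant for site, classes would not be covered.

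The trial exists to decide which components enter the package, and all effects are tested at the same threshold. A standard error that is too small for one component would make that component look better established than the data justify. The article also reuses this model for the secondary outcomes and for acceptability and satisfaction.

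**Working it through.** **Inputs from the document.** N = 500, 250 with and 250 without each component; pre-post correlation 0.65; significance level 0.05 (two-sided is assumed, as sidedness is not stated); stated detectable main effect 0.191 at 80% power.

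**Assumed inputs.** Class size m and ICC are not in the document. The ICC is taken on the baseline-adjusted residual scale, and classes are taken as equal in size and closed.

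**Step 1: reproduce the stated figure.**
- Residual SD = √(1 − 0.65²) = 0.760.
- SE of the main effect with independent women = 0.760 × √(1/250 + 1/250) = 0.0680.
- Power at 0.191 = Φ(0.191/0.0680 − 1.96) = Φ(0.85) = 80.2%.
- Detectable effect at 80% power = (1.960 + 0.842) × 0.0680 = 0.190.
- Interaction as a difference of differences over four cells of 125: SE = 0.760 × √(4/125) = 0.136, and power at 0.382 is again 80.2%.

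So both stated figures assume independent women. Other readings do not match: a one-sided test gives 87.8%, a change score 72.3%, and no baseline adjustment 57.0%.

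**Step 2: allow for clustering in the counselling half only.**
- Variance ratio = {[1 + (m − 1)ICC]/250 + 1/250} ÷ (2/250) = 1 + (m − 1)ICC/2.
- The true SE is 0.0680 times the square root of this ratio.
- Power at 0.191 = Φ(0.191/SE − 1.96); detectable effect = 2.802 × SE.
- Type I error of the unadjusted test = 2[1 − Φ(1.96/√ratio)]. This applies only when class effects are real but average zero.

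| m | ICC | Variance ratio | SE multiplier | Power at 0.191 | Detectable effect | Type I error |
|---|---|---|---|---|---|---|
| any | 0 | 1.000 | 1.000 | 80.2% | 0.190 | 5.0% |
| 10 | 0.01 | 1.045 | 1.022 | 78.5% | 0.195 | 5.5% |
| 10 | 0.02 | 1.090 | 1.044 | 76.8% | 0.199 | 6.0% |
| 10 | 0.05 | 1.225 | 1.107 | 71.9% | 0.211 | 7.7% |
| 10 | 0.10 | 1.450 | 1.204 | 64.6% | 0.229 | 10.4% |
| 8 | 0.05 | 1.175 | 1.084 | 73.6% | 0.206 | 7.1% |
| 15 | 0.05 | 1.350 | 1.162 | 67.7% | 0.221 | 9.2% |

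**Step 3: read the table.** At ICC 0.01 the loss is one to three percentage points of power for classes of 8 to 15. At ICC 0.05 it is roughly 7 to 13 points, and the counselling effect detectable at 80% power no longer lies below 0.2, as the Power analysis section claims for main effects. The calculation ignores dropout and the limited degrees of freedom from a finite number of classes; both would lower power further.

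Only the main effect is quantified. Counselling interactions are affected too where classes are unbalanced on the other factor or class effects differ across its levels. Where each class mixes those levels evenly, an effect common to the whole class largely cancels.

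**The case against.** The strongest objection is that the harm is conditional. Nothing in the document gives an ICC or class size, and at an ICC of 0.01 to 0.02 with classes of 10 the stated figures barely move. That stands. A reader might infer that the standard error is certainly too small; the documents support this only if within-class correlation is positive.

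Second, women are randomised individually. If counselling and class membership changed no woman's activity, the unadjusted test would stay approximately valid, because similarity among women who join at about the same time is shared with concurrent women not assigned to counselling. This stands too: the type I figures need classes with real, differing effects that average zero.

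Third, a reader might infer an unfair advantage over three individually delivered components. The article does not say that supervised exercise is one-to-one, and facility access uses shared venues, so those components may carry some correlation of their own. Selection also follows hierarchical ordering and modified heredity principles from cited sources, not the p-value alone. Omitting a class term does not by itself bias the effect estimate, and a change in the selected package has not been shown.

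Fourth, the article does not say whether classes are closed or rolling, or whether a facilitator stays with a class. Strict nesting is therefore an assumption.

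Finally, one could call this detail for an analysis plan. Degrees-of-freedom methods are such detail. But the article itself settles the clustering question on site grounds and closes the random structure, so an analyst who follows it would fit no class term.

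**Conclusion.** The point holds in conditional form. The plan addresses clustering by site but not by class, and its power figure rests on independent women. If women in the same class are positively correlated, the standard error of the counselling main effect is too small and 80% power at 0.191 is optimistic for that component. The direction is firm under that condition; the size is not fixed by the document. For assumed classes of 10 and an ICC of 0.01 to 0.05, power is about 78% to 72% and the detectable effect 0.195 to 0.211. Type I error can rise to about 6% to 8% when class effects vary around zero.

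A reader might take this to mean that the whole trial is underpowered. It does not: the 0.191 figure is arithmetically correct and remains so for any component without clustering of its own.

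**What to change.** - Record class membership for every woman assigned to counselling, as the classes run, because it may be hard to reconstruct later.
- In the mixed model, add a class random effect that applies only to women assigned to counselling (a partially nested model). If women move between classes, use a multiple-membership form. Keep the participant intercept, and use Satterthwaite or Kenward-Roger degrees of freedom.
- In the Power analysis section, limit the 0.191 figure to components without class clustering. State the counselling detectable effect separately over a declared range of ICC and class size.

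The cost is one data field, a few sentences of text, and a slightly wider interval and slightly less favourable detectable effect for one component. Sample size and delivery of the interventions need not change.

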## Data management

Project data will be entered into an established database developed through RedCap database management software. This software is support by NIH as well as by the Biostatistics Division at UT Southwestern. Relational databases are constructed using a set of two-dimensional tables. Data can be output to standard formats such as Excel, SAS, SPSS. The database will be stored on a secure UT Southwestern network server (backed up nightly) with access limited to project staff. Appropriate procedures safeguard of participant privacy, including data de-identification and SSL encryption for data transfer, will be observed.

## Safety monitoring

Study principal investigators (Drs. [name] and [name]) will meet monthly to examine accumulating data to assure protection of participants’ safety while the study’s scientific goals are being met. These reviews will include an assessment of the possible relatedness of the event to the study intervention or other study procedures. All study staff will be trained in proper event reporting. All protocol deviations and adverse events will be recorded in RedCap. Unexpected serious adverse events potentially related to study procedures will be reported to the UT Southwestern IRB within 5 working days, as will protocol deviations that increase participant risk or compromise data quality.

## Discussion

The purpose of the PACES study is to evaluate multiple strategies for increasing physical activity in breast cancer survivors. Previous studies have identified numerous strategies that can be effective in promoting physical activity among breast cancer survivors. What remains unknown is which strategies are most effective and how these different strategies may interact with each other. Through rigorous evaluation of program outcomes utilizing Multiphase Optimization Strategy, we will be able to identify optimal combinations of intervention components to increase physical activity among breast cancer survivors.

Results of this study will be reported in a peer-review journal. These results will provide in an optimized intervention for increasing physical activity in breast cancer survivors. However, challenges will remain in implementing the optimized intervention for routine use in diverse clinical settings. Future research will be necessary to evaluate strategies for dissemination and implementation to ensure intervention effectiveness.

## Abbreviations

ACS: American Cancer Society
ACSM: American College of Sports Medicine
ALED: Active Living Every Day program
BFI: Brief Fatigue Inventory
BMI: Body Mass Index
CSI: Couples Satisfaction Index
DARS: Dimensional Anhedonia Rating Scale
EVS: Exercise Vital Sign
FACT-B: Functional Assessment of Cancer Therapy – Breast
IPAQ: International Physical Activity Questionnaire
IRB: Institutional Review Board
MOST: Multiphase optimization strategy
MVPA: Moderate-to-vigorous physical activity
NCCN: National Comprehensive Cancer Network
PACES: Promoting Activity in Cancer Survivors
PAR-Q: Physical Activity Readiness Questionnaire
P-FIBS: Pain – Frequency, Intensity, and Burden Scale
PSQI: Pittsburgh Sleep Quality Index
QIDS-SR: Quick Inventory of Depressive Symptomatology – Self-Rated
